#### 8.4 Study flow chart(s) / table of study procedures and assessments

[figure not shown]

| Study procedures                                                             | Assessments                                       |
|------------------------------------------------------------------------------|---------------------------------------------------|
| High-flow nasal cannula therapy with 70 l/min with 100% oxygen, jaw thrust   | Cerebral NIRS                                     |
| High-flow nasal cannula therapy with 70 l/min with 100% oxygen, laryngoscopy | transcutaneous CO 2 and O 2 |
| Medium-flow nasal cannula therapy with 10 l/min with 100% oxygen             | Time                                              |
| Low-flow oxygen 100% through standard nasal cannula, 2 l/min                 | Saturation                                        |
|                                                                              | Post-medication interview                         |
|                                                                              | EIT                                               |
|                                                                              | Narcotrend™                                       |

|  |                                                   |
|--|---------------------------------------------------|
|  | TOF                                               |
|  | Arterial blood gas analyses                       |
|  | Airway patency using nasopharyngeal
fiberscope |
|  | etCO 2                                 |

## 8.5 Assessments of outcomes

### 8.5.1 Assessment of primary outcome

Transcutaneous CO2 will be measured throughout the study period by TCM4, Radiometer™, Thalwil, Switzerland; by applying a probe over the patient's chest. This is a standard procedure used very often during anaesthesia without complications.

Increase in ptcCO2 in mmHg/min will be calculated by dividing the difference of ptcCO2 by the time of the measurement, once linear increase has set in. In our pilot study, we have found transcutaneous ptcCO2 to have a little delay (about 60-90 seconds) after which linear rise sets in.

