| Outcome(s):   | 
Primary outcome: mean ptcCO2 increase in mmHg/min during apnoea time, measured transcutaneously.
 
Secondary outcomes: in case of desaturation within the predefined apnoea time: time (in seconds) until desaturation from SpO2 100% to 92%, measured by pulse oximetry. Changes in ptcO2, paO2 and paCO2 in mmHg/min, blood gas analysis parameters, upper airway patency, influence of jaw thrust vs. continuous laryngoscopy on CO2 clearance during HFNCT, changes in brain oxygenation (measured by near infrared spectroscopy (NIRS)) during apnoea time, changes in electrical impedance tomography (EIT) to validate ventilatory effect and pulse contour analysis to monitor cardiac output.
 |
| Study design: | 
Prospective, single centre, randomised controlled trial with four groups:
 

1) high flow 70 l/min of oxygen, using jaw thrust

2) high flow 70 l/min using continuous laryngoscopy

3) medium flow 10 l/min using jaw thrust

4) low flow 2 l/min using jaw thrust

                                                                                                                                                                                                                                                                                                                                                                                                                                                                                     |

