## **5. STUDY OUTCOMES**

### **5.1 Primary Outcome**

Primary outcome: increase of  $p_{tc}CO_2$  level in mmHg/min during apnoea.

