### **6.2.2 Blinding procedures**

Patients are under general anaesthesia therefore blinded to the treatment group, but due to the different oxygen delivery systems study personnel in the operating theatre cannot be blinded.

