### 10.2 Determination of Sample Size

We assumed that with maximal flow of 70L O2/min and maximal mouth opening, there would be the least increase of  $p_{tc}CO_2$ /min. Patel et al. showed an increase of only 1.13mmHg using this technique [2]. However, this was  $etCO_2$  instead of  $p_{tc}CO_2$ . According to Gustafson et al., who measured  $p_{tc}CO_2$  as well as  $p_aCO_2$ , the  $CO_2$  increase was in fact 1.8mmHg/min, with a standard deviation of 0.35mmHg [3]. This correlated very well with our own findings in our pilot study (not published).

Using a non-inferiority design, a difference of means of 0.3mmHg/min, a standard deviation of 0.35mmHg/min, an alpha of 0.025 (one-sided) and a power of 80%, the necessary sample

size calculates to 22 patients per group. Therefore, we will include 25 patients in each group to account for possible drop outs. A value of 0.3mmHg/min would still only result in a difference in increase of 9mmHg in 30 minutes of apnoea time. We defined this as measurable, but still clinically acceptable, because the normal range of standard arterial pCO2 is 11mmHg (35-46 mmHg) [6].

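### The primary endpoint is a two-point slope with no fixed start, and its time window is worded differently in Section 8.5.1 and in the outcome statements

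*Protocol*

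**What the plan says.** Section 8.5.1 is the only place in the protocol that gives a calculation. The ptcCO2 difference is divided "by the time of the measurement, once linear increase has set in". The reason given is a pilot observation: the transcutaneous reading was found "to have a little delay (about 60-90 seconds) after which linear rise sets in". No start time, linearity criterion or assessor is named.

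The outcome statements are shorter. The synopsis has the mean ptcCO2 "increase in mmHg/min during apnoea time, measured transcutaneously". Section 5.1 has the increase of the ptcCO2 "level in mmHg/min during apnoea". Neither mentions leaving out the lag.

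Section 6.2.2 says that "study personnel in the operating theatre cannot be blinded", and Section 6.3 calls the study open. No blinded reading of the traces is described. The synopsis and Section 6.1 have ptcCO2 measured continuously. Section 6.1 allows a run to end before 15 min on SpO2, ptcCO2, pH or potassium limits.

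**The concern.** The margin is 0.3 mmHg/min on an expected rate of 1.8, so a rule that moves individual values by tenths of a unit matters. Three places describe the single primary endpoint, and they can be read as two different windows. Inside the narrower window the start is still open.

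Two consequences follow. First, a start placed before the true onset includes flat trace and makes the CO2 rise look slower, the more so the shorter the run. If short runs or early starts were commoner in one arm, that arm would look better than it is, which in a non-inferiority trial is the anti-conservative direction. Second, two readings carry much less information about a slope than the continuous trace that is being measured anyway.

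**Working it through.** **Inputs.** Margin 0.3, SD 0.35, one-sided alpha 0.025, power 80%, expected rate s = 1.8 mmHg/min, 25 patients per group (Section 10.2). Delay d = 1.0 to 1.5 min (Section 8.5.1). Longest run 15 min (Sections 6.1 and 8.5.2). The 5 min run and all other short runs are illustrations.

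**The plan's own figure.** Section 10.2 uses "Using a non-inferiority design, a difference of means of 0.3mmHg/min" and "a standard deviation of 0.35mmHg/min, an alpha of 0.025 (one-sided) and a power of 80"%. n = 2 × [0.35 × (1.960 + 0.842) / 0.3]² = 21.4, so 22 per group. This reproduces and is not in dispute.

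**Model (an assumption).** The trace is flat for d minutes, then linear at s. A two-point slope from time a ≤ d to the end T equals s(T − d)/(T − a). A start at or after onset returns s, so the error runs only downwards.

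**Start choice inside 8.5.1** (start 60 s, onset 90 s):

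- 15 min: 1.8 × 13.5/14 = 1.736, shift 0.064 (21% of the margin)
- 5 min: 1.8 × 3.5/4 = 1.575, shift 0.225 (75%)
- 4 min: 1.8 × 2.5/3 = 1.50, shift 0.30 (100%)

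**Whole lag included** (a = 0, shift = s·d/T):

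| Run | 60 s lag | 90 s lag |
|---|---|---|
| 15 min | 0.12 (40%) | 0.18 (60%) |
| 10 min | 0.18 (60%) | 0.27 (90%) |
| 5 min | 0.36 (120%) | 0.54 (180%) |

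The shift equals the margin at T = 1.8 × d/0.3, that is 6 min (60 s lag) or 9 min (90 s lag).

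**From one patient to the arm comparison.**

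- *Lag included in all arms, every run 15 min.* A true difference of 0.30 becomes 0.30 × 14/15 = 0.28 or 0.30 × 13.5/15 = 0.27. The standard error at 25 per group is 0.35 × √(2/25) = 0.099. Holding the SD at 0.35, the one-sided error at a true difference of 0.30 rises from 2.5% to P(Z > 1.96 − 0.02/0.099) = 3.9% or P(Z > 1.96 − 0.03/0.099) = 4.9%.
- *Lag included, run length differs, equal true slopes, 90 s lag.* An arm running 10 min gives 1.53 against 1.62 for a 15 min control, a difference of −0.09. An arm running 5 min gives 1.26 against 1.62, or −0.36.
- *Start choice differs systematically by arm, towards non-inferiority.* A bias of 0.064 gives P(Z > 1.96 − 0.064/0.099), about 9%. Biases of 0.12 and 0.18 give about 23% and 44%.
- *Start error unrelated to arm* (uniform over 0-90 s, 90 s lag, 15 min). This adds an SD of 0.052. √(0.35² + 0.052²) = 0.354, and n stays at 22.

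**Precision** (assumed independent reading noise σ of 1-2 mmHg; the protocol gives none). The two-point SE over 13.5 min is σ√2/13.5 = 0.105 to 0.210. For least squares on 28 readings at 30 s, Sxx = 0.5² × 28 × (28² − 1)/12 = 456.75, so the SE is σ/√456.75 = 0.047 to 0.094. Autocorrelated readings would reduce the gain.

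**The case against.** **Label and calculation.** The synopsis and Section 5.1 name the outcome, while 8.5.1 says how to compute it and deliberately leaves the delay out. Reading 8.5.1 as a refinement is natural, and this largely stands. The mismatch is something to reconcile, not a flat contradiction. The 40-60% figures describe a window that 8.5.1 itself excludes; the looseness inside 8.5.1 is worth about 21% of the margin at 15 min.

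**Cancellation.** A shift in one patient's value is not a shift in the treatment difference. With a common rule and similar run lengths most of it cancels. This also stands, apart from the modest shrinkage if the lag is included.

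**Short runs.** The protocol gives no share of early stops, and Section 2.1.2 regards low-flow desaturation as a small risk. Nor is the ptcCO2 limit a likely cause at the planning rate. From 46 mmHg (the top of the normal range in Section 10.2), 1.8 × 15 = 27 brings the value to 73, below 80. Reaching 80 in 5 min would need (80 − 46)/5 = 6.8 mmHg/min. A 5 min run at 1.8 would have to end on another criterion.

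**Left to a statistical analysis plan.** One slope per patient compared by t-test is an accepted method, equal weighting is not an error, and an onset algorithm could sit in a later document. But 8.5.1 already fixes the estimator as a single difference over time, so this is more than missing detail.

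**Inferences to avoid.** A reader might conclude that unblinded staff judge the onset by eye. The protocol does not say how or by whom the onset is found, and Section 6.2.2 speaks only of theatre personnel. A reader might also conclude that two-point noise makes the SD of 0.35 too small. Section 10.2 takes that SD from a cited study's measured rates; it may already contain reading noise, and the documents do not show how those rates were computed.

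**Conclusion.** The point holds as one of definition and estimation. The primary endpoint rests on two readings and an unfixed start, and the outcome statements do not carry the exclusion of the lag. For a single patient the size is about 0.06 mmHg/min at 15 min and 0.23 at 5 min within 8.5.1. It is 0.12-0.18 at 15 min if the whole lag is included, and then exceeds the margin in runs shorter than 6-9 min. These figures rest on a flat-then-linear trace at 1.8 mmHg/min.

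Bias in the comparison from start choice or run length needs a difference between arms. The open design and the early-stop criteria permit one, but the protocol does not quantify it, so the 9-44% error rates are conditional and not a forecast. It would be wrong to read the 60% figure as movement of the treatment effect. The loss of precision from two readings is roughly a factor of two under the assumed noise. The plan should be changed because a better rule is available at little cost, not because the comparison is shown to be biased.

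**What to change.** Put one definition in the synopsis, Section 5.1 and Section 8.5.1: the least-squares slope, in mmHg/min, of all recorded ptcCO2 values from a fixed time after the start of apnoea that lies beyond the stated lag (for example 2 min) to the end of apnoea. Compute it by script from the device record, identically in all arms, so that nobody who knows the allocation chooses the start.

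Keep the two-point value as a sensitivity analysis. Keep the mixed-effects regression of Section 10.3.1 in that role too; fitted to the repeated readings, it weights short runs by the information they carry. Making it primary is not needed to cure the problem.

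The cost is a wording change, a short script, and making sure that the continuous trace is exported and kept. The first 2 minutes no longer contribute, and very short runs still give imprecise slopes, or none if they end before the fixed start, so the text should say how such runs are handled.

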### 8.5.2 Assessment of secondary outcomes

Time to desaturation below 92% will be measured using a stopwatch. If desaturation does not set in, the experiment will end once 15 minutes have been completed.

Arterial blood pressure will be measured using a catheter in the radial artery. ECG and pulse oximetry will also be measured. These measurements are normal anaesthesia care.

From the arterial catheter blood samples will be drawn for blood gas analyses.

Brain oxygenation as a surrogate of brain perfusion will be assessed by cerebral NIRS, using Niro-200NX (Hamamatsu, Tokyo, Japan) monitor continuously. This is also a standard procedure without complications, especially during cardiac surgery.

EIT will be continuously measured using PulmoVista® 500 by Dräger, Lübeck, Germany, to visualize possible atelectasis and its progression over time.

EIT is a non-invasive, radiation-free technique for the assessment of spatial and temporal ventilation distribution based on the changes in electrical properties of the tissue during the respiratory cycle. EIT measurements will be performed using a commercially available setup (PulmoVista 500, Draeger, Germany). A loose-fitting belt with 16 evenly spaced electrodes will be placed around the participant's chest in thoracic median plane. Small electrical currents are injected through adjacent electrodes in a rotating mode. Resulting potential differences are measured, and impedance distribution sampled at 30 Hz will be calculated by an automated linearised newton-raphson reconstruction algorithm [19]. Relative change in end-expiratory lung impedance (EELI) and measures of ventilation inhomogeneity such as the global inhomogeneity index (GI) will be calculated as described previously using customized software (Matlab R2013a, The MathWorks Inc., Natick, MA, USA) [20, 21].

After securing the airway, the highest etCO2 measured during the first minute will be recorded.

### 8.5.3 Assessment of safety outcomes

NIRS registers alterations in cerebral blood flow and perfusion. Arterial blood gas analysis will detect severe acidosis or hyperkalaemia.

#### 8.5.3.1 Adverse events

Any adverse events during the study period will be recorded.

An **Adverse Event (AE)** is any untoward medical occurrence in a patient or a clinical investigation participant administered a pharmaceutical product, and which does not necessarily have a causal relationship with the study procedure. An AE can therefore be any unfavourable and unintended sign (including an abnormal laboratory finding), symptom, or disease temporally associated with the use of a medicinal (investigational) product, whether or not related to the medicinal (investigational) product. [ICH E6 1.2]

A **Serious Adverse Event (SAE)** is classified as any untoward medical occurrence that:

- results in death
- is life-threatening
- requires in-patient hospitalization or prolongation of existing hospitalisation
- results in persistent or significant disability/incapacity
- is a congenital anomaly/birth defect

In addition, important medical events that may not be immediately life-threatening or result in death, or require hospitalisation, but may jeopardise the patient or may require intervention to prevent one of the other outcomes listed above should also usually be considered serious. [ICH E2A].

All SAEs will be reported immediately and within a maximum of 24 hours to the Sponsor-Investigator of the study.

SAEs resulting in death are reported to the local Ethics Committee within 15 days.

SUSARs will be reported to the local Ethics Committee within 15 days.

#### 8.5.3.2 Laboratory parameters

Arterial blood for blood gas analysis will be drawn awake, immediately after apnoea sets in, after one minute of apnoea and thereafter every two minutes. All in all, this makes ten blood gas analysis, for each of which we need to draw about 7.5 ml of blood. This is a study related measurement and not part of normal workflow.

Parameters analysed will include:

- pH
- $p_a\text{CO}_2$
- $p_a\text{O}_2$
- Saturation
- base excess
- bicarbonate
- potassium

#### 8.5.3.3 Vital signs

During anaesthesia, standard monitoring of vital signs will be recorded, as defined by the American Society of Anesthesiologists and the Swiss Society for Anaesthesia and Resuscitation. This includes: EKG, end-tidal  $\text{CO}_2$ , continuous arterial blood pressure through

arterial catheter, pulse oximetry, body temperature.

## 8.6 Procedures at each visit

First visit during pre-anaesthesia visit to rule out exclusion criteria and to obtain written informed consent and to complete any missing data from the pre-operative interview. A follow-up visit will be performed (structured post-medication interview) before discharge. This includes asking for possible side effects: sore throat/nose, mandibular pain, nausea, dental damages, oropharyngeal injuries of any kind, headaches as well as nasal dryness.

## 9. SAFETY

Adverse events during the anaesthesia procedure will be treated according to current departmental guidelines at the discretion of the attending anaesthesia consultant.

Overall very little risk is involved for the patients, as apnoeic oxygenation has been shown to work in routine patient care.

Also, arterial blood gas analysis will be conducted every two minutes to ensure stable pH and potassium levels.

The study can be terminated at any time points without delay and the airway can be secured immediately.

## 10. STATISTICAL METHODS

### 10.1 Hypothesis

Null hypothesis: The difference of the mean increase of  $p_{tc}CO_2$  between any of the three intervention groups and the control group is at least 0.3 mmHg/min, the control group being lower.

Primary hypothesis: the difference of the mean increase of  $p_{tc}CO_2$  between the groups is less than 0.3 mmHg/min (non-inferior margin), one-sided testing. This hypothesis was based on a small clinical pilot study that showed no differences regardless of flowrate or mouth opening (jaw-thrust vs. laryngoscopy).

Secondary outcome hypothesis: The number of patients not tolerating the apnoea time of 15 minutes is not significantly higher in any of the three intervention groups.

Secondary outcome hypothesis: no significant changes in vital parameters such as cerebral perfusion will be recorded.

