### **4.3 Secondary Objectives**

Secondary study objective is to evaluate the mean duration of apnoea. Also, changes in EIT, NIRS, BP and heart rate are measured. We will also assess airway patency while performing jaw thrust. This can be either patent or not-patent.

We also want to monitor the effect of increased  $CO_2$  on the cardiac output via the simultaneously obtained pulse contour analysis using either FlowTrac by Edwards Lifescience, Irvine, California, or LiDCO by LiDCO Ltd, London, UK.

Bilateral frontal cerebral NIRS measurements will be performed to determine the effect of high  $CO_2$  on brain perfusion. A NIRO monitor by Hamamatsu, Japan, will be used, which delivers brain oxygenation as a surrogate of brain perfusion, as well as the percentage of oxygenated and deoxygenated blood in the sampled tissue.

To ensure absence of respiratory movements, complete neuromuscular blockage will be confirmed using train-of-four (TOF) which should be 0 throughout the experiment. Additional muscle relaxants may be administered if necessary. Respiration must be avoided at all times, since otherwise our results would be unusable.

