Overall, we will include 100 patients, 25 per group. Patients will be blinded as to their group allocations. Double-blinding is not possible, as devices differ from each other.

This design allows us to focus our study on the primary outcome, since we ensure, that free air circulation (and possible CO2 clearance) is possible by visually assessing airway patency. Through measurement of extended vital parameters, we can identify physiologic influence of rising CO2 in anaesthetized patients undergoing apnoeic oxygenation.

In addition, demographic data will be extracted from the AIS. This only includes standard data, that is collected through routine normal clinical workflow, such as age, sex, weight, height, BMI, airway risk factors, underlying diseases, smoking habits, ASA physical health status and indication for the surgery.

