### **10.3 Planned Analyses**

#### **10.3.1 Datasets to be analysed, analysis populations**

Distribution of data will be checked using qq-plots and swilk command in stata, normal distributed data will be presented as means and standard deviation, otherwise median and interquartile range will be used. Proportions will be presented as numbers and percentage. Analytical statistics uses Mann-Whitney u-tests and Students t-test, according distribution, or ANOVA and Kruskal-Wallis for multiple groups. Each of the groups will a-priori be compared to the control group independently, without correction of multiple comparisons. Other multiple comparisons or subgroup-analyses will be performed using correction factors. Proportions will be compared by Chi-square tests or Fisher's exact test. As sensitivity analyses, we will do regression analyses, using mixed effects linear regressions.

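### Two secondary hypotheses are met by non-significance alone at 25 per arm, so a 20-point excess of apnoea failures could satisfy one of them; seconds to desaturation is defined only in patients who desaturate

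*Protocol*

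**What the plan says.** Section 10.1 sets a non-inferiority margin of 0.3 mmHg/min for the primary outcome. Below it stand two secondary hypotheses without a margin: "The number of patients not tolerating the apnoea time of 15 minutes is not significantly higher in any of the three intervention groups", and "no significant changes in vital parameters such as cerebral perfusion will be recorded".

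Section 10.2 derives the sample size from the CO2 slope only: 22 per group, raised to 25. Section 6.1 confirms this: "Overall, we will include 100 patients, 25 per group".

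Section 10.3.1 names the tests: "Proportions will be compared by Chi-square tests or Fisher's exact test". It gives no rule for choosing between them, and no sidedness or significance level for secondary outcomes. Each intervention arm is "compared to the control group independently, without correction of multiple comparisons".

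The synopsis defines the time outcome as "in case of desaturation within the predefined apnoea time: time (in seconds) until desaturation" from SpO2 100% to 92%, and section 5.2 adds a similar proviso that it may not occur. Section 8.5.2 says that without desaturation the experiment ends at 15 minutes. Section 4.3 separately states: "Secondary study objective is to evaluate the mean duration of apnoea".

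**The concern.** A hypothesis worded as the absence of significance is supported by a small sample as readily as by a true absence of harm. The protocol avoids this for CO2 by setting a margin, but not for apnoea tolerance or vital parameters.

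This matters because prolonging apnoea is part of the overall objective (section 4.1). Section 2.1.1 argues that a non-inferior result could favour wide use of lower-flow devices, and section 2.1.2 concedes that desaturation in the low-flow groups cannot be fully excluded. If low flow were reported as not worse tolerated merely because p exceeded 0.05, that argument would gain support it had not earned.

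The time outcome has a different weakness. Seconds to desaturation exist only for patients who desaturate, and the allocated flow may affect who they are. A comparison of those times would lose the protection of randomisation. An arm with one early desaturation could look worse than an arm with ten later ones.

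**Working it through.** **Inputs.** 25 per arm (section 6.1); chi-square or Fisher (section 10.3.1); each arm compared with control without correction (section 10.3.1). The protocol gives no control failure rate, so the rates below are assumptions. Failure is taken to mean apnoea stopped before 15 minutes. The level is taken as two-sided 5% unless stated.

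**1. The plan's own figure.** For the primary outcome,
n = 2 × (1.960 + 0.842)² × 0.35² / 0.3² = 21.4, rounded up to 22 per group. This agrees with section 10.2. No corresponding calculation exists for the failure proportion.

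**2. One observed table: control 2/25 (8%), intervention 7/25 (28%), difference 20 points.**

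- Fisher: the probability of 7 or more of the 9 failures falling in the intervention arm is [C(25,7)·C(25,2) + C(25,8)·C(25,1) + C(25,9)] / C(50,9) = 173,292,350 / 2,505,433,700 = 0.069. The two-sided p is 0.138.
- Uncorrected chi-square: the pooled proportion is 9/50 = 0.18; SE = √(0.18 × 0.82 × 2/25) = 0.1087; z = 0.20/0.1087 = 1.84; two-sided p = 0.066.
- Newcombe 95% interval: the Wilson limits are 0.022 to 0.250 for 2/25 and 0.143 to 0.476 for 7/25.
  Lower: 0.20 - √[(0.28 - 0.143)² + (0.250 - 0.08)²] = -0.018.
  Upper: 0.20 + √[(0.476 - 0.28)² + (0.08 - 0.022)²] = +0.404.

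The stated hypothesis would be met, yet the data would be compatible with an excess of up to 40 points.

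**3. Other tables with the same 20-point excess.**

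| Control v intervention failures | Two-sided Fisher p | Uncorrected chi-square p | Newcombe 95% CI (points) |
|---|---|---|---|
| 0 v 5 | 0.0502 | 0.018 | +2.6 to +39.1 |
| 1 v 6 | 0.098 | 0.042 | +0.1 to +39.7 |
| 2 v 7 | 0.138 | 0.066 | -1.8 to +40.4 |
| 5 v 10 | 0.217 | 0.123 | -5.3 to +42.2 |

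In the first two rows the conclusion depends on which permitted test is used. In the last two, neither two-sided test reaches 5%.

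**4. Power for a true 20-point excess.** Power is the sum, over all tables with more failures in the intervention arm and p < 0.05, of the product of the two binomial probabilities (n = 25 each).

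| Assumed control v intervention rate | Power, two-sided Fisher | Power, uncorrected chi-square |
|---|---|---|
| 0% v 20% | 38% | 77% |
| 10% v 30% | 30% | 45% |
| 20% v 40% | 23% | 35% |

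The chance of not finding a significant increase is the complement: 62%, 70% and 77% by Fisher, or 23%, 55% and 65% by chi-square, per comparison.

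**5. The time outcome.** No arithmetic is needed. The synopsis and section 5.2 give the outcome a value only where desaturation occurs. Section 6.1 lets apnoea end for other reasons (ptcCO2, pH, potassium or the time limit), and those patients have no value.

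**The case against.** - **Test choice.** The clearest-looking example, 0 v 5, is a knife-edge. It is non-significant only just by two-sided Fisher (0.0502), and uncorrected chi-square (0.018) or one-sided Fisher at 5% (0.025) would flag it. This stands, so the point should not rest on that table. Expected failures per arm there are 2.5, and in 2 v 7 they are 4.5; below 5, convention favours Fisher. Because the hypothesis is directional, a one-sided chi-square at 5% would also flag 2 v 7 (0.066/2 = 0.033), though not 5 v 10 (0.123/2 = 0.061).
- **Status.** These are secondary hypotheses, numbers and percentages will be shown, and nowhere does the protocol say that p > 0.05 will be reported as equivalence. This limits the consequence but does not repair a criterion that is itself worded as non-significance.
- **Inferred analysis.** No section says that seconds will be compared among desaturating patients only, and censoring rules are commonly left to an analysis plan. Lowest saturation is also recorded whether or not a patient desaturates. This stands in part: the comparison is an inference, but the conditional definition is the protocol's own.
- **Stronger readings.** A reader might infer that multiplicity correction makes these hypotheses still easier to meet. Section 10.3.1 does not support that, since comparisons with control are uncorrected. A reader might also infer that the mean duration of apnoea in section 4.3 is invalid because of censoring. It is not: each patient's apnoea ends at a stop criterion or at 15 minutes, so the duration is fully observed and its average is a legitimate restricted mean.

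**Conclusion.** The point holds for the wording of section 10.1 and for the definition of time to desaturation.

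The tolerance hypothesis can be met despite an observed 20-point excess of failures. This is so by two-sided Fisher for all four tables shown, and by two-sided uncorrected chi-square for 2 v 7 and 5 v 10. It is a statement of what could happen, not of what always would: with 0 or 1 control failures the result turns on the test. The power figures rest on assumed control failure rates.

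The hypothesis on vital parameters shares the logical fault, but the calculations on proportions do not measure its size. The conditional time outcome is a separate, smaller weakness, because the tolerance hypothesis itself counts all patients. The primary margin and sample size are untouched. The change should be made, but it does not threaten the main result.

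**What to change.** - **Section 10.1.** Replace both secondary hypotheses by estimation. Give the difference from control in the proportion stopped before 15 minutes, and in the proportion with SpO2 below 92%, each with a Newcombe 95% interval. Give mean changes in NIRS and vital signs with 95% intervals. State that p > 0.05 will not be taken to show equal tolerance or no change.
- **Section 5.2 and synopsis.** Define time to SpO2 below 92% for all randomised patients, and analyse it as cumulative incidence to 15 minutes with the other protocol stops as competing events.
- **CRF.** Record which criterion ended apnoea. Section 8.5.2 provides a stopwatch time, but the protocol does not say that the reason is captured.

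**Cost.** Text changes, one CRF item and slightly more analysis, with no extra patients and no change to clinical rules. The intervals will be wide and will not support a firm claim of equal tolerance.
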